#### Inclusion criteria

Patients must meet all of the following criteria to be enrolled in this trial:

Age: 5 to 55 years (inclusive);BCVA: Interocular difference of 0.2 logMAR or more, with BCVA in the AE < 1.0 logMAR and BCVA in the better eye within age-normal limits;Risk factors of amblyopia, such as anisometropia, strabismus, deprivation;Patients with deprivation amblyopia must have undergone surgical interventions to address the underlying structural causes of deprivation (e.g., cataract extraction with intraocular lens implantation, ptosis correction surgery, etc.);Optical refractive correction in full time, if needed, for no less than 3 months;Orthotropia (orthotropia with refractive correction or after strabismus surgery) or intermittent exotropia with good fusional control;No ongoing or other planned amblyopia treatment (except spectacles).

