### Sample size {14}

According to the requirements of the Good Clinical Practice for Medical Devices ([2022] No. 28) and the Guidance for the Design of Medical Device Clinical Trials, sample size estimation will be performed referring to the clinical study results of comparable medical devices of the investigational medical device and clinical expert opinions.

In this study, the sample size will be calculated based on the primary endpoint, namely the total effective proportion at 13 weeks, using the superiority design. Considering the treatment effects are strongly age-dependent, the participants are divided into 2 groups based on ages: Subgroup I (aged 5 to under 18 years) and Subgroup II (aged 18 to under 55 years).

Subgroup I: Based on clinical expert opinions and preliminary study results (unpublished data), the anticipated effective proportion at 13 weeks of the intervention group will be 75%, while that of the control group, based on previous literatures [10, 21, 22] and clinical expert opinions, will be 40%. With a superiority margin of 0 and a 1:1 ratio of intervention group to control group, the sample size required for each group is 28, as calculated using the PASS 2022 software, at the 5% significance level (two-sided) with 80% power. Considering the 15% dropout proportion during the study, 33 patients will be included in the intervention group and the control group, respectively, in patients aged 5 to under 18 years.

Subgroup II: Based on expert opinions and preliminary study results (unpublished data), the anticipated effective proportion at 13 weeks of the intervention group will be 60%, while that of the control group, based on previous literature [23, 24] and clinical expert opinions, will be 20%. With a superiority margin of 0 and 1:1 ratio of intervention group to control group, the sample size required for each group is 20 as calculated using the PASS 2022 software, at the 5% significance level (two-sided) with 80% power. Considering the 15% dropout proportion during the study, 24 patients will be included in the intervention group and the control group, respectively, in patients aged 18 to under 55 years.

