## Assignment of interventions: allocation

### Sequence generation {16a}

With age (5– < 18 years old, 18– < 55 years old) as a stratified factor, patients will be assigned sequentially into “intervention group” and “positive control group,” according to the randomization sequence generated by the statistician using the PROC PLAN procedure in SAS at a 1:1 ratio.

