### Implementation {16c}

With age (≥ 18 years old, < 18 years old) as the stratified indicator, all eligible patients who had signed the written informed consent after a detailed explanation about the trial were randomly divided into two groups respectively named “AR training group” and “positive control group,” at a 1:1 ratio according to the randomization sequence generated by the statistician.

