## Statistical methods

### Statistical methods for primary and secondary outcomes {20a}

The normal quantitative variables will be described as the mean and standard deviation (SD), and other quantitative variables will be described using the median and interquartile range. Categorical variables are described as the number of cases and the percentage of each category. Independent-sample T test or Wilcoxon rank-sum test will be used for the comparison between groups of quantitative variables based on the data distribution characteristics, and chi-square test or exact probability test will be used for categorical variables.

Statistical analysis will be performed using the SAS 9.4 (or above). Unless specified, all statistical tests will be two-sided at the 5% significance level, and the difference is considered statistically significant when the p value is ≤ 0.05. The analysis will be performed on an intention-to-treat and also per-protocol approaches. No interim analyses are planned.

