#### Analysis of primary endpoint

For the evaluation of the primary efficacy endpoint, the effective propotions (Wilson 95% CIs) and the between-group difference in effective proportions (Newcombe 95% CIs) at 13 weeks within Subgroups I and II are calculated. If the lower limit of the 95% CIs for the between-group difference in effective proportions within Subgroups I and II are > 0, then superiority is established. Primary analysis will calculate clinical response rates (Wilson 95% CIs) and rate differences (Newcombe 95% CIs) for treatment vs. control arms in Groups I/II at Week 13. Cochran-Mantel–Haenszel (CMH) analysis stratified by center will provide MH-adjusted proportion differences with 95% CIs for between-group comparisons. For the primary efficacy endpoint, results based on both the full analysis set (FAS) and per protocol set (PPS) are provided.

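### Continuous secondary endpoints are compared without baseline or age-stratum adjustment, and the centre-stratified CMH analysis does not name age: a modest loss of precision, not a bias

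*Protocol article*

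**What the plan says.** **Randomisation.** Age group is the only factor named. Sequence generation {16a} reads "With age (5– < 18 years old, 18– < 55 years old) as a stratified factor"; Implementation {16c} reads "With age (≥ 18 years old, < 18 years old) as the stratified indicator". Neither section, nor Trial design {8}, names centre as a factor, although four centres take part. Sample size {14} gives the reason for splitting by age: "Considering the treatment effects are strongly age-dependent".

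**Primary endpoint.** Under Analysis of primary endpoint, the responder proportions and their between-arm difference ("Newcombe 95% CIs) at 13 weeks within Subgroups I and II are calculated") are obtained separately in each age subgroup, and the superiority rule uses those within-subgroup limits. The same section adds a CMH analysis: "analysis stratified by center will provide MH-adjusted proportion differences with 95% CIs for between-group comparisons". It does not say whether this is run within each age subgroup or over all ages together.

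**Secondary endpoints.** The Secondary outcomes section defines the visual-function measures as mean changes between baseline and week 13, and lists the measurements at weeks 2, 4 and 9 as material for studying change within a person. Analysis of secondary endpoints refers back to the general methods in {20a}: "Independent-sample T test or Wilcoxon rank-sum test will be used for the comparison between groups of quantitative variables", with the choice between the two depending on how the data are distributed. No baseline covariate or age term is named. Methods for additional analyses {20b} plans analyses of primary and secondary outcomes by age subgroup.

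**Age range.** Inclusion criteria admit patients aged "5 to 55 years (inclusive").

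**The concern.** A change score subtracts the baseline in full. Unless baseline and follow-up are perfectly correlated, that over-corrects, and the leftover noise widens the interval. Every patient's baseline acuity, contrast sensitivity and age group will be on file, so the unadjusted comparison gives up precision that costs nothing to keep. With about 48 evaluable patients per arm (28 + 20), that precision is worth having. Letting the data choose between a t test and a rank test also leaves the estimand of each secondary comparison open until the data are seen.

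The CMH analysis raises a smaller issue. Analyses normally reflect the factors used to randomise. Here the one named stratifier is not a stated randomisation factor, and the one stated factor, across which the protocol itself expects different response rates, is left out unless the analysis is run within age subgroups.

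**Working it through.** **1. The protocol's own figures.** Inputs from Sample size {14}: responder rates 75% v 40% (under 18) and 60% v 20% (adults), two-sided 5%, 80% power, margin 0, 15% dropout. With the protocol's formula, (1.960 + 0.842)² = 7.849:

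- Subgroup I: 7.849 × (0.40×0.60 + 0.75×0.25) / 0.35² = 7.849 × 0.4275 / 0.1225 = 27.39, so 28; 28/0.85 = 32.9, so 33.
- Subgroup II: 7.849 × (0.20×0.80 + 0.60×0.40) / 0.40² = 7.849 × 0.40 / 0.16 = 19.62, so 20; 20/0.85 = 23.5, so 24.
- Total: 2 × (33 + 24) = 114.

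All stated figures reproduce, so the planned rates can be used below.

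**2. Continuous secondary endpoints.** Let s² be the variance at each visit (taken as equal) and ρ the correlation between baseline and week 13. Per patient:

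- change score: 2s²(1 − ρ)
- ANCOVA on baseline: s²(1 − ρ²)
- ratio: (1 − ρ²) / [2(1 − ρ)] = (1 + ρ)/2

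The protocol gives no ρ, so a range is assumed:

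| ρ (assumed) | ratio | variance saved | equivalent extra patients (1/ratio − 1) |
|---|---|---|---|
| 0.5 | 0.75 | 25% | 33% |
| 0.7 | 0.85 | 15% | 18% |
| 0.8 | 0.90 | 10% | 11% |

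Any gain from the age-stratum term comes on top. It cannot be sized because the protocol gives no age-specific figures for these endpoints.

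**3. The CMH analysis, if pooled over ages.** Take 28 + 20 evaluable per arm at the planned rates. A crude all-ages comparison stands in for a centre-stratified one, which assumes that centre itself carries no information.

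- All-ages rates: (28×0.75 + 20×0.60)/48 = 0.6875 and (28×0.40 + 20×0.20)/48 = 0.3167; difference 0.371.
- Crude variance: (0.6875×0.3125 + 0.3167×0.6833)/48 = 0.00898; SE 0.0948.
- Age-stratified variance: (28/48)² × 0.4275/28 + (20/48)² × 0.40/20 = 0.00520 + 0.00347 = 0.00867; SE 0.0931.
- Ratio 0.965, so about 3.5% less variance. Approximate power is 97.5% crude and 97.8% stratified.

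The point estimate is 0.371 either way.

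**4. Bias.** Allocation is 1:1 within age group, so at 33/33 and 24/24 the age mix is the same in both arms and the shift from ignoring age is zero. If the split drifted to 31 v 35 children out of 57, the crude difference would move by −(2/57) × (0.15 + 0.20) = −0.012, where 0.15 and 0.20 are the planned child-adult gaps in each arm (75 − 60 and 40 − 20 points).

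**5. Stratum wording.** Inclusion criteria include age 55. Sample size {14} and Sequence generation {16a} end the adult group below 55. Explanation for the choice of comparators {6b}, Implementation {16c} and Methods for additional analyses {20b} use 18 and over.

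**The case against.** **The primary analysis already handles age.** This stands in full. A reader might infer from the centre-only CMH sentence that the plan ignores its stratification factor; the superiority rule works inside each age subgroup, and {20b} repeats the subgroup split for secondary outcomes. Adding age to the primary rule would change nothing.

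**Confounding by age.** A reader might also infer that a centre-only estimate mixes age into the treatment effect, since ages are not balanced within centres. A 60/40 split of children between arms in one centre would indeed shift that centre's difference by 0.2 × 15-20 = 3-4 points. But with four equal centres that is about 1 point overall, and because child numbers are balanced across the trial, an excess in one centre is roughly offset in the others. The documents support a precision argument only.

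**The CMH analysis may be within age subgroup.** The sentence follows directly on one about the two age groups and does not say pooled. If it is within subgroup, the age point falls away, and the remaining question is sparseness: four centres sharing 28 or 20 per arm average 7 or 5 patients per arm each. Stratifying by centre is not in itself an error.

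**The unadjusted tests are valid, and ANCOVA suits few endpoints.** Both are right. Worth-4-dot and Bagolini results are categorical, stereoacuity moves in discrete steps, and adherence and adverse events have no meaningful pre-treatment value. The gain applies mainly to habitual-corrected acuity and contrast sensitivity.

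**An analysis plan not shown may add covariates.** It may, but the protocol does not leave the method open: it names the unadjusted tests and applies them to the secondary endpoints.

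**Conclusion.** The point holds as one about efficiency and clarity. For the continuous secondary endpoints with a usable baseline, the stated tests give up 10-25% of variance, equivalent to about 11-33% more patients, if the baseline-to-week-13 correlation lies between 0.8 and 0.5 and the variances at the two visits are similar. For the CMH analysis the loss is about 3.5% of variance, and only if it pools the ages. The primary conclusion is unaffected, and neither analysis is biased by leaving age out.

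The age-range mismatch is a genuine but minor wording conflict. A reader might infer that an eligible 55-year-old cannot be randomised; three other sections place such a patient in the adult stratum, so the documents show an inconsistency, not a gap in allocation.

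**What to change.** - **Continuous secondary endpoints** (mainly habitual-corrected acuity and contrast sensitivity): replace the choice between t and Wilcoxon tests with ANCOVA on the baseline value and age stratum, or a repeated-measures model over weeks 2, 4, 9 and 13 with the same terms. The latter also serves the stated interest in change over time. Keep the present methods for categorical outcomes.
- **CMH analysis:** state whether it is run within each age subgroup or over all ages. If over all ages, add age group as a stratum and report the centre-stratified result as a sensitivity analysis.
- **Adult stratum:** reconcile the two descriptions with the eligibility range, and confirm which one the randomisation system applies.

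The cost is wording in the protocol or analysis plan. Age, baseline and visit data are already scheduled in Table 1. Trial status reports 43 of 114 patients enrolled, no interim analysis is planned, and all analysis follows trial closure, so the change can be made before any comparison by arm is seen.

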#### Analysis of secondary endpoints

The secondary efficacy endpoints are analyzed based on the FAS and PPS. The statistical methods for secondary efficacy endpoints follow the general principles of statistical analysis described above.

#### Analysis of safety endpoints

Safety endpoints are analyzed based on the safety set (SS). The occurrence type, frequency, severity, correlation with the investigational device of adverse events, and device deficiencies during the trial will be listed, and between-group comparisons are conducted using the chi-square test or Fisher's exact test.

#### Analysis datasets

Three statistical datasets will be used in this clinical trial. The efficacy analysis will be carried out on the basis of FAS and PPS; all baseline demographic data analysis will be performed on FAS; and the safety evaluation will be conducted on the SS.FAS: refers to all participants who have signed the informed consent and are randomly enrolled to participate in the treatment according to the ITT principle;PPS: a subset of the FAS, generally referring to participants who complete the evaluation on the primary endpoint based on the FAS without major protocol violations;SS: all enrolled cases who have already used the device and undergone safety evaluation are included in the SS, regardless of whether they have completed the entire follow-up plan or not.

### Interim analyses {21b}

There are no interim analyses planned.

### Methods for additional analyses (e.g., subgroup analyses) {20b}

The subgroups (aged 5 to < 18; ≥ 18) will be analyzed in both primary and secondary outcomes to test the consistency. The statistical methods follow the general principles of statistical analysis described above.

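### The age-subgroup analysis is meant to test consistency of effect, but the method it names tests for zero effect within each age group and never compares the two effects

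*Protocol article*

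**What the plan says.** All references are to the protocol article.

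- **Methods for additional analyses {20b}** gives the aim: the two age subgroups "will be analyzed in both primary and secondary outcomes to test the consistency". The next sentence gives the method: "The statistical methods follow the general principles of statistical analysis described above".
- **Statistical methods {20a}** holds those principles. For quantitative outcomes, "Independent-sample T test or Wilcoxon rank-sum test will be used for the comparison between groups of quantitative variables"; for the rest, "chi-square test or exact probability test will be used for categorical variables". Both compare AR training with patching.
- **Analysis of primary endpoint** already works by age group: effective proportions and their Newcombe-interval differences "at 13 weeks within Subgroups I and II are calculated". Its superiority condition begins "If the lower limit of the 95% CIs for the between-group difference in effective proportions within Subgroups I and II are > 0". The one stratified analysis is by center, not age: a Cochran-Mantel-Haenszel "analysis stratified by center will provide MH-adjusted proportion differences with 95% CIs for between-group comparisons".
- **Sample size {14}** calls treatment effects strongly age-dependent and sizes each age group separately, "at the 5% significance level (two-sided) with 80% power".

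**The concern.** Consistency across age groups is a statement about two effects: its null hypothesis is that the AR-minus-patching difference is the same in both. A t test, Wilcoxon test, chi-square test or exact test run inside one age group has another null hypothesis, that the difference there is zero. Putting two such p-values side by side does not turn them into a test of equality. With small strata, one p-value can fall below 0.05 and the other above it through chance alone.

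Section {20b} does more than announce a subgroup analysis and leave the details open. It states an aim and names a method that cannot serve it, and a statistical analysis plan that followed the wording faithfully would carry the mismatch forward. The question matters for interpretation, because the trial spans ages 5 to 55 and is stratified and sized on the premise that response depends on age.

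**Working it through.** **Inputs (Sample size {14}).** Subgroup I: 75% v 40%, 28 evaluable and 33 enrolled per arm. Subgroup II: 60% v 20%, 20 evaluable and 24 enrolled per arm. Two-sided 5%, 80% power, margin 0, 15% dropout.

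**1. The plan's own figures.** With the protocol's formula, n = (1.960 + 0.842)² × [Pc(1−Pc) + Pt(1−Pt)] / (Pt−Pc)²:
- Subgroup I: 7.849 × (0.2400 + 0.1875) / 0.35² = 27.39, so 28; 28/0.85 = 32.9, so 33.
- Subgroup II: 7.849 × (0.1600 + 0.2400) / 0.40² = 19.62, so 20; 20/0.85 = 23.5, so 24.

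All agree with the protocol.

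**2. Chance of discordant subgroup results when the true effects are equal.** Let p1 and p2 be the probabilities that the Newcombe lower limit exceeds 0 in Subgroups I and II. They come from exact binomial enumeration, with control rates 40% and 20% and the same true risk difference added in both. The age groups are independent, so P(exactly one significant) = p1(1−p2) + p2(1−p1).

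| Common difference | 33/24 per arm: p1, p2 | Exactly one | 28/20 per arm: p1, p2 | Exactly one |
|---|---|---|---|---|
| 20 points | 0.414, 0.333 | 47% | 0.307, 0.290 | 42% |
| 25 points | 0.580, 0.468 | 51% | 0.454, 0.408 | 49% |
| 30 points | 0.736, 0.609 | 45% | 0.613, 0.531 | 49% |
| 35 points | 0.860, 0.739 | 33% | 0.763, 0.648 | 42% |
| 40 points | 0.940, 0.844 | 20% | 0.882, 0.753 | 31% |
| 45 points | 0.981, 0.919 | 10% | 0.957, 0.841 | 19% |
| 50 points | 0.997, 0.964 | 4% | 0.990, 0.908 | 10% |

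Worked line, 35 points at 33/24: 0.860 × 0.261 + 0.739 × 0.140 = 0.328. As a rough cross-check, 80% power in both groups gives 2 × 0.8 × 0.2 = 32%. With no effect in either group the figure is about 5%.

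**3. Quantitative secondary outcomes.** The protocol gives no effect sizes, so these are assumptions. Noncentral-t power at 33 and 24 per arm is 0.516 and 0.396 for a common 0.5 SD (discordance 50%), and 0.893 and 0.774 for 0.8 SD (discordance 28%).

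**4. What a direct comparison offers.** The SE of the difference between the two risk differences, at the design rates, is √[(0.1875 + 0.2400)/n1 + (0.2400 + 0.1600)/n2]:
- 33/24: 0.172; 95% CI half-width 34 points; 80% power needs 2.802 × 0.172 = 48 points.
- 28/20: 0.188; half-width 37 points; 80% power needs 2.802 × 0.188 = 53 points.

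Under equal effects a Wald test of this contrast rejected about 6% of the time in simulation at 33/24, close to its nominal 5%.

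**The case against.** The strongest reply is that nothing in the protocol says one significant and one non-significant age group means inconsistency. That is correct. A reader might infer that the plan will declare identical effects inconsistent 20% to 50% of the time, but the document does not support that. The figures describe one natural reading of the prescribed tests, and only for common differences of about 20 to 40 points. The Newcombe intervals also let a reader compare the two estimates informally.

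A second reply is that discordant verdicts on the primary endpoint come from the superiority rule and would be just as frequent after any change to {20b}. This also stands. That rule answers a different question and is not faulted here.

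A third is that an interaction analysis is detail that belongs in an unseen statistical analysis plan. This holds only in part. Silence would be acceptable, and a further test there is not excluded. But {20b} is not silent: it ties the aim to named methods that do not address it.

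A fourth is that the interaction estimate will seldom be conclusive. That is true, and it is the reason to ask for an estimate with an interval and not a verdict from a p-value. Nor is effect modification by age among the stated objectives, which limits the weight of the point.

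**Conclusion.** The mismatch is real. The stated aim is consistency, the stated method tests zero effect within each age group, and the effects are nowhere compared. It concerns interpretation only; randomization, sample size and the primary decision rule are untouched.

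If consistency is read from significance, equal effects at the planned sizes would give a discordant pair 33% (35 points) or 20% (40 points) of the time with 33/24 per arm, and 42% or 31% with 28/20. This rests on the protocol's control rates, on equality measured on the risk-difference scale, and on a reading rule that the protocol does not state. At 45 points the rate is about 10% to 19%, and at 50 points 4% to 10%. The secondary-outcome figures are illustrations under assumed effect sizes.

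**What to change.** Revise {20b} as follows.

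- **Primary endpoint:** report the Subgroup I risk difference minus the Subgroup II risk difference, with a 95% CI, as the consistency analysis. This keeps to the protocol's own scale; a Breslow-Day or logistic interaction test works on the odds-ratio scale and answers a different question.
- **Quantitative secondary outcomes:** report the treatment-by-age-stratum interaction estimate with a 95% CI from a linear model.
- **Categorical secondary outcomes:** use the same difference-of-risk-differences contrast.
- **Reading:** keep the within-age-group results as description, and state that neither discordant subgroup p-values nor a non-significant interaction settles consistency.

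Leave the superiority rule as it is. The cost is a few sentences and little programming, with no new data. At the reported status 43 of 114 patients were enrolled and no interim analysis is planned, so the change can be made before results are seen. The price is imprecision: the interval will be about ±34 to 37 points wide on the primary endpoint, and the text should say so.
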